### Primary and secondary outcomes (Table 2)

2.5

*Sleep Outcomes:* To determine if CBT-I in individuals with MS improves insomnia symptoms and sleep quality (Aim 1), insomnia severity is assessed using the Insomnia Severity Index (ISI) [35], sleep quality is assessed using the Pittsburgh Sleep Quality Index (PSQI) [44], and actigraphy is used for objective assessment of sleep outcomes:

1.The Insomnia Severity Index (ISI) [35] is used to assess insomnia symptoms. The ISI is used to determine eligibility (described above under “Screening Procedures”). Because the ISI determines insomnia symptoms for 2 weeks and baseline assessment is completed within 2 weeks of screening procedures, the ISI from screening is used as the baseline assessment of insomnia symptoms.2.Self-reported sleep quality is indexed using the Pittsburgh Sleep Quality Index (PSQI) [44]. The PSQI consists of 9 items within 7 sleep categories and is a well-validated and reliable measure of sleep quality. The 7 sleep category scores are summed to form a single global score ranging from 0 to 21, with a global score of >5 reflecting poor sleep quality [44].3.Participants wear an actigraph on their non-dominant wrist for 7 days and nights. An instructional handout is mailed with the actigraph detailing proper fit and safety information (i.e. remove the actigraph if there is skin irritation or if increases difficulty sleeping). A postage-paid envelope is included for participants to return the actigraph. The outcomes of interest for actigraphy are sleep efficiency and total sleep time, and we will explore wake after sleep onset, number of awakenings, sleep latency, time in bed, and sleep duration variability.

*Fatigue and Health-related Quality of Life Outcomes:* To determine if CBT-I in individuals with MS improves fatigue and health-related quality of life (Aim 2), fatigue is assessed using the Modified Fatigue Impact Scale (MFIS) [45] and the Fatigue Severity Scale (FSS) [46] and health-related quality of life is assessed using the Multiple Sclerosis Impact Scale (MSIS-29) [47].1.The MFIS assesses the impact of fatigue on daily activities for the previous month. The MFIS consists of 21 items with 3 subscales: physical, cognitive, and psychosocial. Scores ranging from 0 to 84, a higher score indicates a greater impact of fatigue.2.The FSS consists of 9 questions and assesses the impact of fatigue on activities for the week prior. The mean of the 9 scores is calculated, ranging from 0 to 7. The MFIS and FSS are both valid and reliable measures of self-report fatigue [48].3.The MSIS-29 assesses health-related quality of life in the past 4 weeks, consisting of 29 with subscales of physical (20 items) and psychological (9 items). The total score ranges from 0 to 100, and higher scores indicate worse quality of life due to physical and physiological impacts of MS.

*Secondary Outcomes:* To explore the characteristics of participants that predict improvement in sleep outcomes (Exploratory Aim 3), disability (assessed by the Patient-Determined Disability Steps; PDDS) [32], depression (assessed by the Patient Health Questionnaire; PHQ-9) [41], anxiety (assessed by the Generalized Anxiety Disorder Assessment; GAD-7) [49], sleep self-efficacy (assessed by the Sleep Self-Efficacy Scale; SESS) [50], and adherence to the intervention are also assessed. Disability level, depression, anxiety, and sleep self-efficacy have a known bidirectional relationship with sleep and fatigue and are plausible predictors of responders and non-responders to CBT-I.1.Patient-Determined Disability Steps (PDDS) [32] scale is used to assess disability. It consists of a 9-point scale ranging from “normal” (score of 0) to “bedridden” (score of 8). The PDDS has been validated and highly associated with the Expanded Disability Status Scale [33].2.Patient Health Questionnaire (PHQ-9) [41] is a valid and reliable method to assess depression during the past 2 weeks. It consists of 9 items with a score ranging from 0 to 27. A tenth question that is not included in the summary score assesses how depressive symptoms affect functional level. The PHQ-9 is used as a screening tool and an outcome measure.3.Generalized Anxiety Disorder Assessment (GAD-7) [49] is a valid and reliable method to assess anxiety over the past 2 weeks. This questionnaire consists of 7 items, and the score from each item is summed for an overall score ranging from 0 to 21 with a higher score indicating a higher level of anxiety. An additional eighth question assesses if anxiety impacts daily activities and sociability.4.Sleep Self-Efficacy Scale (SESS) [50] is a 9-item self-report questionnaire used to measure sleep self-efficacy. The respondents indicate confidence in ability to accomplish 9 sleep behaviors on a 5-point Likert scale with 1 = “not confident” at all to 5 = “very confident”. The score ranges from 0 to 45 with a higher score indicating greater sleep self-efficacy.5.Adherence to CBT-I intervention: To assess adherence to the CBT-I intervention, the sleep log is used to assess number of mornings per week the participant got out of bed at agreed upon time, number of times got out of bed if unable to sleep within 20 min, and number of nights per week the participant conducted wind-down routine. A total percentage will be calculated and used as the outcome of interest.

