### Sample size justification

3.1

We will enroll 70 participants (35 in each of the two groups) in our study. Our sample size calculations are guided by effect size estimates for the primary outcome of ISI and PSQI from our pilot studies [28,29]. We hypothesize that CBT-I will perform better than the Control group for ISI and PSQI. Our hypotheses are – $H_{0}:\mu_{CBT-I}\leq \mu_{Control}$ vs $H_{0}:\mu_{CBT-I}>\mu_{Control}$ where the μ represents the mean scores of the two arms at 6 week and 6 month assessment after adjusting for the baseline.

Our calculations are purposely done in a conservative way considering the following two limitations of our pilot study comparing CBT-I to an Active Control and to a brief education group (BE) – {i} Our preliminary study was a pilot study with only 10 subjects in the CBT-I, Active Control and BE arms, and {ii} There was no significant difference in the Active Control vs BE arm for both the primary and secondary outcomes in our pilot study. Thus, we have made the following assumptions in the power analysis calculations for the proposed study – {i} The higher of the mean change scores of the Active Control and BE arm in the pilot study is considered as $\mu_{Control}$, {ii} The mean change score for CBT-I in the pilot study is considered as $\mu_{CBT-I}$, {iii} The higher of the two standard deviations (of effect size) for the CBT-I and Control group is used as the common standard deviation, {iv} sample size calculations are done with a two-sided test, with type I error set at 5 % and target power is taken as 90 %.

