A ‘*Repeated Measures design’* with autocorrelation of ρ=0.5 (between the 6 week and 6 month assessment) and a type I error of 5 % was used to conduct the sample size calculations. With the assumptions mentioned above, for the *primary outcome of ISI*, a sample size of 17 in each of the two arms (n = 34 total) is required to detect a $\mu_{CBT-I}$ value of 13.8 versus $\mu_{Control}$ value of 8.1 (with common standard deviation σ=5.8) with 90 % power. Analogously, in the case of *primary outcome of PSQI*, a sample size of 25 in each of the two arms (n = 50 is required to detect a $\mu_{CBT-I}$ value of 6.7 versus $\mu_{Control}$ value of 4.6 (with common standard deviation σ=2.6) with 90 % power. Thus, max (34, 50) = 50 is chosen. The attrition rate from our prior preliminary efficacy trials of CBT-I in people with MS were: 16.7 % in-person CBT-I [28], 9.1 % in brief education [28], and 0 % in tele-health delivered CBT-I [29]. To be cautious, we will anticipate an attrition rate of 25 % due to the delayed reassessment, and so 50/0.75 ≈ 67 (rounded up to 68) is chosen. Looking at overall capability at enrolling participants, we have decided to enroll a total of 70 subjects in our study. We used the *‘Test for Two Means in a Repeated Measures Design’* platform in PASS 2020 to conduct our sample size calculations.

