#### Exploratory Aim 3: To explore the baseline characteristics of participants that predict improvement in sleep outcomes

3.2.3

HypothesisBaseline disability level, anxiety, depression, and sleep self-efficacy will predict responders and non-responders (i.e. higher disability, anxiety, and depression, lower sleep self-efficacy, and lower intervention adherence will predict non-responders; lower disability, anxiety, and depression, and higher sleep self-efficacy and level of intervention adherence will predict responders).

*Statistical Plan*: For Aim 3, the outcome is dichotomous (responders vs non-responders) and a logistic regression analysis will be conducted modeling responder status (defined as meeting the minimal clinically important difference of ≥ 6 points on the ISI) at 6 weeks. This will allow assessment of the effect of baseline predictors such as disability level, anxiety, depression, sleep self-efficacy level, and intervention adherence. The analysis will be conducted at the 5 % level of significance.

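### Aim 3 logistic regression: five predictors against about 2 to 3 expected non-responders in CBT-I, or 12 to 16 with both arms pooled

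*Protocol article*

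**What the plan says.** Section 3.2.3 (Exploratory Aim 3) dichotomises the ISI change at 6 points, measured at 6 weeks, and states that "a logistic regression analysis will be conducted modeling responder status". The predictors it lists are "disability level, anxiety, depression, sleep self-efficacy level, and intervention adherence", and testing is at the 5% level. A directional hypothesis is given for each predictor. The section does not say whether one arm or both enter the model, and it gives no expected number of non-responders.

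Section 2.5 says that disability, depression, anxiety and sleep self-efficacy "are plausible predictors of responders and non-responders to CBT-I". The fifth predictor, adherence, is defined there and in Table 2 only for the CBT-I programme, from sleep-log items such as keeping the agreed rising time.

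Section 3.1 supplies the planning values: "We will enroll 70 participants (35 in each of the two groups) in our study"; mean ISI changes of 13.8 (CBT-I) and 8.1 (control), "with common standard deviation σ=5.8"; and 25% attrition, attributed to the late follow-up visit.

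**The concern.** A logistic model is limited by the size of its smaller outcome group. The trial is planned on a mean CBT-I improvement more than twice the responder threshold, so few CBT-I participants should fall below that threshold, and five predictors are then spread over very few non-responders. Two failures are possible. In the first, a combination of predictors separates responders from non-responders completely or nearly so (or there are no non-responders at all), and the maximum-likelihood estimates are not finite. In the second, the model fits but exaggerates the odds ratios and its own discrimination.

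At stake is the credibility of Aim 3 alone; the primary ISI comparison is untouched. It still matters, because the Introduction and Discussion say these results should help clinicians and patients choose a sleep intervention.

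**Working it through.** **Inputs (section 3.1 unless noted).** The two planning means are change scores: "The mean change score for CBT-I in the pilot study is considered as" the CBT-I value, and "The higher of the mean change scores of the Active Control and BE arm in the pilot study is considered as" the control value. So CBT-I mean 13.8, control mean 8.1, common SD 5.8, 35 per arm, 25% attrition. Responder cut 6 points, five predictors (section 3.2.3).

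**The plan's own figure first.** For the average of two visits correlated 0.5, the variance is 5.8² × (1 + 0.5)/2 = 25.23. With two-sided 5% and 90% power:

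n per arm = 2 × (1.960 + 1.282)² × 25.23 / (13.8 − 8.1)² ≈ 16.3, rounded up to 17.

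This matches the stated 17. The same formula gives the stated 25 for PSQI, and 50/0.75 gives 67. The inputs are therefore being read as the protocol uses them.

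**Expected non-responders, assuming normal change scores.**

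- CBT-I: P(change < 6) = Φ((6 − 13.8)/5.8) = Φ(−1.345) = 0.089
- Control: P(change < 6) = Φ((6 − 8.1)/5.8) = Φ(−0.362) = 0.359

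| Analysed per arm | CBT-I | Control | Both arms | Per predictor, CBT-I | Per predictor, both |
|---|---|---|---|---|---|
| 35 (no attrition) | 3.1 | 12.6 | 15.7 | 0.6 | 3.1 |
| 26 (25% attrition) | 2.3 | 9.3 | about 11.7 | 0.5 | 2.3 |

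The binomial chance of 3 or fewer non-responders in CBT-I is 62% with 35 analysed and 80% with 26.

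**Sensitivity.** Letting the CBT-I mean run from 10 to 13.8 and the SD from 4 to 7, the expected CBT-I count runs from about 1 to 10, which is at most about 2 per predictor.

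**Does a finite estimate exist in CBT-I alone?** Trials were simulated with all five predictors entered together, and separation was checked by linear programming. Predictor strength and correlation are assumptions, because the protocol gives neither.

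- Uncorrelated predictors, continuous change: no finite estimate in 27% (n = 35) and 47% (n = 26) when no predictor has an effect; 51% and 71% when each predictor correlates 0.3 with change.
- Predictors correlated 0.3 with each other, joint correlation with change 0 to 0.6, continuous change: 27 to 46% (n = 35) and 50 to 70% (n = 26).
- The same, with change rounded to whole points as the ISI is scored: about 34 to 53% (n = 35) and 56 to 74% (n = 26).

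Rounding moves the effective cut to 5.5 and lowers the CBT-I non-responder probability to 7.6%, so the rounded runs carry slightly fewer events than the table. Taken together, the range is roughly 25 to 55% at n = 35 and 50 to 75% at n = 26.

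**Both arms pooled.** Separation is rare: under 1% with five predictors, and 2 to 10% in runs with four predictors plus a treatment term. Overfitting remains. With 52 analysed and joint correlation 0.4, the mean log odds ratio is 0.27 against a true 0.20, with root mean squared error 0.61. Firth estimation gives a mean of 0.21 and an error of 0.46. When no predictor has any effect, the apparent area under the ROC curve is still 0.72.

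**The case against.** The strongest reply is that the article does not specify the model being criticised. It says logistic regression and introduces the predictors as examples; it does not say unpenalised, maximum likelihood or joint entry. A condensed article may leave the estimator to the analysis plan, and Firth estimation is still logistic regression. This stands in part: unpenalised joint entry is the plain reading, not a stated one. But the outcome cut, the five predictors and the test level are all fixed, and together they fit poorly with the sample-size figures in the same document.

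Further points that stand:

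- The arm is not stated. The section 2.5 wording and the CBT-I-only adherence measure point to CBT-I alone, but the wording is background rationale and covers only four of the five predictors.
- The 25% attrition belongs to the 6-month visit, while Aim 3 uses 6 weeks. Pilot CBT-I attrition was 0% and 16.7%. So 26 analysed is a worst case.
- The planning means and SD come from pilot arms of 10.
- The aim is labelled exploratory throughout.

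A reader might infer that the Aim 3 estimates will be undefined, or that maximum likelihood usually fails here. The documents do not support that. Non-existence is a risk confined mainly to a CBT-I-only model, and it exceeds one half mostly near 26 analysed or with strong predictors. A reader might also infer that Aim 3 will by itself determine individual treatment; the article claims only that it will help guide the choice.

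**Conclusion.** The concern holds in this limited form. On the protocol's own planning values, Aim 3 sets five predictors against about 2 to 3 non-responders in CBT-I, or about 12 to 16 in both arms. Restricted to CBT-I, a standard fit carries roughly a one-in-four to one-in-two risk of having no finite estimate at 35 analysed, and one-in-two to three-in-four at 26. Pooled, the fit nearly always exists but overstates effects and discrimination.

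This rests on normal change scores, on the planning means and SD holding in the trial, on joint entry of all five predictors, and on the assumed predictor correlations in the simulations. Within the sensitivity range examined, the CBT-I count stays at or below about 2 per predictor. The exploratory label limits the seriousness but does not cure the problem, since directional hypotheses and a 5% test are attached. The change is worth making before the analysis.

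**What to change.** In section 3.2.3:

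1. Fit the model by Firth penalised likelihood (the FIRTH option of SAS PROC LOGISTIC), with profile penalised-likelihood confidence intervals.
2. State the number of non-responders expected from the planning values. Because this differs about fivefold between CBT-I alone (2.3 to 3.1) and both arms (11.7 to 15.7), say which participants the count refers to.
3. Present the odds ratios with their intervals as exploratory estimates.

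Entering the predictors one at a time is optional: it eases the burden on so few events but gives up mutual adjustment among related predictors.

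The cost is a few sentences and one option in software the protocol already names; design and data collection do not change. The downside is slight shrinkage of odds ratios towards 1. Firth estimation makes the estimates finite and less biased, but it does not create information: with 2 to 3 non-responders the intervals will remain wide.

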### Reassessments

2.6

Participants undergo reassessment of the primary and secondary outcomes (Table 2) after the 6-week intervention and 6 months following completion of interventions (Fig. 2). Similar to the baseline assessment, participants are emailed a link to complete the assessment questionnaires and mailed the actigraph with a postage-paid envelope to return the actigraph.

**Table 2 tbl2:** Primary and secondary outcomes.

Sleep Outcomes: (Aim 1)
1. Insomnia Severity Index (ISI) [35] (primary outcome)
2. Pittsburgh Sleep Quality Index (PSQI) [44]
3. Actigraphy
Fatigue and Quality of Life Outcomes: (Aim 2)
1. Modified Fatigue Impact Scale (MFIS) [45]
2. Fatigue Severity Scale (FSS) [46]
3. Multiple Sclerosis Impact Scale (MSIS-29) [47]
Secondary Outcomes: (Exploratory Aim 3)
1. Patient-Determined Disability Steps (PDDS) [32]
2. Patient Health Questionnaire (PHQ-9) [41] to assess depression
3. Generalized Anxiety Disorder Assessment (GAD-7) [49]
4. Sleep Self-Efficacy Scale (SESS) [50]
5. Adherence to CBT-I protocol (*Gathered from sleep log*: number of days/week got out of bed at agreed upon time, number of times got out of bed if unable to sleep within 20 min, number of nights/week conducted wind-down routine; a percentage will be calculated)

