#### Cognitive behavioral therapy for insomnia (CBT-I)

2.7.1

The CBT-I program is a 1x/week, 6-week one-on-one program via video conferencing (HIPAA-compliant Zoom). The program is based on standard CBT-I manuals [51,52]. Participants maintain a sleep diary during the program to aid in tailoring the program. Each session includes a summary and graphing of sleep diary data, an assessment of treatment gains and adherence, and determination if upward titration of total sleep time is warranted. The general session outlines are as follows with each session lasting 45–60 min:

*Session 1*: subjective sleep history and description of current sleep issues, education regarding physiological mechanisms of sleep using the two process of model of sleep [53] and 3P model of insomnia [54], and tailored sleep promotion techniques, collaboratively set time in bed restriction, discuss strategies for stimulus control (if fall risk, perform counter-control in bed instead), discuss avoiding/limiting naps (limit napping to ≤ 30 min, to take the nap as early in the day as possible, and delaying bedtime to a later time may be necessary until they were adequately tired).

*Session 2*: review sleep promotion techniques, introduce diaphragmatic breathing and deep breathing as relaxation techniques to reduce pre-sleep arousal.

*Session 3*: introduce mindfulness as a technique to reduce pre-sleep arousal.

*Session 4*: introduce progressive muscle relaxation (PMR) as relaxation technique to reduce pre-sleep arousal (if concern about contraction portion of PMR may increase symptoms or spasticity, recommend only performing relaxation strategies).

*Session 5*: cognitive restructuring for negative sleep beliefs as needed, reinforce and/or continue to tailor various techniques.

*Session 6*: discuss relapse prevention and maintenance of sleep gains.

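### The adherence percentage does not score whether time in bed stayed within the agreed window, so a participant who goes to bed early every night can still score 100%

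*Protocol article*

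**What the plan says.** Section 2.5 (Secondary Outcomes, item 5) of the protocol article defines adherence from the sleep log. The first item is rise time: "the sleep log is used to assess number of mornings per week the participant got out of bed at agreed upon time". The second is stimulus control: "number of times got out of bed if unable to sleep within 20 min". The third is "number of nights per week the participant conducted wind-down routine". They are combined into one figure: "A total percentage will be calculated and used as the outcome of interest". Table 2 lists the same three items. Neither place gives weights, denominators or a cut-off.

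Section 2.7.1 describes the treatment. Session 1 includes the step "collaboratively set time in bed restriction". Every session reviews and graphs the diary, assesses adherence, and decides whether to titrate upward. Section 2.7.2 names time-in-bed restriction as one of five active components withheld from the control group, without ranking them. On the data source, section 2.7.1 says: "Participants maintain a sleep diary during the program to aid in tailoring the program".

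Section 3.2.3 (Exploratory Aim 3) enters intervention adherence as a predictor in a logistic regression of ISI response at 6 weeks. Section 2.6 says: "Participants undergo reassessment of the primary and secondary outcomes (Table 2) after the 6-week intervention and 6 months following completion of interventions". Adherence is one of the outcomes in Table 2.

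**The concern.** A time-in-bed window has two ends. The score checks when the participant gets up but not when they went to bed, nor how long they stayed in bed in total. The restriction is delivered in session 1, and its loosening is considered at every later contact, yet departures from it at the bedtime end leave no direct trace in the percentage.

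What is at stake is the reading of Aim 3. The plan expects higher adherence to predict response. If participants who kept the window and participants who did not can hold the same score, the fitted coefficient describes adherence to rise time, stimulus control and wind-down, not to the programme as delivered. A weak association could then be reported as showing that adherence to CBT-I does not matter, although one component was never measured against its target.

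**Working it through.** There is no planned figure to reproduce; the point concerns how a measure is built.

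**Step 1: components delivered against components scored.**

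| Element | In the treatment | In the adherence percentage |
|---|---|---|
| Agreed rise time (one end of the window) | implied by the restriction, 2.7.1 | yes |
| Bedtime end, or total time in bed against the window | session 1, reviewed each session, 2.7.1 | no |
| Stimulus control | session 1, 2.7.1 | yes (getting out of bed) |
| Wind-down routine | not named in the session outlines | yes |

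Time in bed appears elsewhere only as an exploratory actigraphy variable (section 2.5), recorded for 7 days at each assessment. It is not said to be compared with the agreed window.

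**Step 2: score as written.** Let r, s and d be the proportions achieved on rise time, stimulus control and wind-down. Taking s as a proportion of the occasions when it applied is an assumption, because the article gives no denominator. With equal weights (also an assumption):

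score = 100 × (r + s + d) / 3

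- Pattern A, only the bedtime end ignored: r = s = d = 1, so 100 × 3/3 = 100%.
- Pattern B, stimulus control ignored as well: 100 × (1 + 0 + 1)/3 = 66.7%. If counts are pooled instead, 3 missed get-ups a week give 14/(14 + 3) = 82.4%, and 7 give 14/21 = 66.7%.
- Pattern C, only the wind-down kept: 100 × (0 + 0 + 1)/3 = 33.3%.

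Pattern A does not depend on the weights: any weighted average of three full marks is 100%. Patterns B and C show that the score does fall when the other elements are ignored.

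**Step 3: size of the departure that goes unseen.** As an illustration only, assume an agreed window from 00:00 to 06:00, which is 6 h. A participant in bed from 22:00 to 06:00 spends 8 h in bed; 8/6 = 1.33, or 33% over the window. The rise-time item still reads 7/7. The total stays at 100% as long as the other two items are also met.

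**Step 4: score with the missing item.** Let w be the proportion of logged nights within the window:

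score = 100 × (r + s + d + w) / 4

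For pattern A with w = 0, this is 100 × 3/4 = 75%. For a participant who keeps everything, it remains 100%. The two are now distinguishable. Reported side by side instead, pattern A would read 100% on the existing score and 0% on the window.

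**The case against.** The strongest reply is that the restriction is not absent from the score. The agreed rise time is one end of the window, and someone who goes to bed too early and lies awake without getting up may lose marks on the stimulus-control item. That stands: the restriction is partly captured, and 100% requires full marks on the other items too. It does not close the gap, because someone who goes to bed early and falls asleep, or who gets up each time as instructed, loses nothing.

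Several stronger readings are tempting, and the article does not support them:

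- A reader might infer that the score misses the main dose of CBT-I. Section 2.7.2 lists five active components and ranks none.
- A reader might infer that under-treated participants are classed as adherent. There is no cut-off; the result is a percentage.
- A reader might infer that the Aim 3 association is necessarily pulled towards zero. That needs an error structure which the article does not give, and it offers no correlation between the score and window adherence from which to size any effect.
- A reader might infer that attendance goes unrecorded. It is an operational record that a condensed article commonly leaves to the full protocol, so its absence here is no defect.
- A reader might infer that a 6-month adherence value is impossible. Section 2.6 covers all Table 2 outcomes, while the diary is described only for the programme weeks. However, Fig. 2, which sets out the assessment time points, is not shown, and no stated analysis uses a 6-month adherence value.

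The argument that the whole matter belongs in an unseen document does not stand: section 2.5 and Table 2 both fix the components explicitly.

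**Conclusion.** The concern holds in a limited form. The adherence percentage is defined in two places and omits adherence to the time-in-bed window, which the programme sets in session 1 and reviews throughout. Full marks are possible without ever keeping the bedtime end of that window; this follows from the definition under any weighting. The drop to 75% once the item is added assumes equal weights and a participant who never keeps the window.

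The consequence is an incomplete predictor in exploratory Aim 3. A reader might be tempted to carry this over to the efficacy conclusions, but the Aim 1 and Aim 2 models in sections 3.2.1 and 3.2.2 do not use adherence, so the primary ISI result is untouched. The 6-month mismatch is a minor point of wording, because Aim 3 models response at 6 weeks.

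**What to change.** - From the diary already kept, derive the percentage of logged nights on which time in bed stayed within the window agreed at the preceding session. Either add it as a component of the adherence percentage or report it alongside. Keep the three existing items, and make the same change in section 2.5 and Table 2.
- Report sessions attended out of 6 descriptively.
- Reconcile section 2.6 with section 2.7.1 on whether adherence is collected at 6 months and, if so, from what source.
- While the definition is open, reconcile the stimulus-control item with the fall-risk modification in section 2.7.1. A participant following that modification stays in bed, whereas the item counts getting out of it.

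The cost is small: the agreed window has to be recorded at each session, and one more variable derived. This assumes that the sleep log and the sleep diary are the same instrument and that it records bedtime and rise time, which the article implies but does not state.

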While CBT-I is a first-line recommended behavioral intervention for insomnia according to guidelines from the American College of Physicians [25], the European Sleep Research Society [26], and the American Academy of Sleep Medicine [27], there are limited studies that have examined the effect of CBT-I on sleep outcomes and comorbid MS symptoms. We recently completed the first pilot randomized controlled trials to assess feasibility and preliminary efficacy of CBT-I modified specifically for pwMS [28,29]. Modifications that we made to the standard CBT-I program include: 1. For individuals who felt a nap was necessary for their health and wellbeing, the recommendation to avoid naps was modified to limit napping to ≤30 min, to take the nap as early in the day as possible, and delaying bedtime to a later time may be necessary until they were adequately tired; 2. For individuals with functional or mobility limitations or those who had concerns about falls (either individual or CBT-I provider), stimulus control was modified to perform a relaxation or distraction technique in bed; 3. For individuals who were concerned that the contraction portion of progressive muscle relaxation (PMR) might exacerbate spasticity (despite the standard instruction to gently tense muscle groups without causing discomfort), PMR was modified to focus solely on the relaxation component (i.e., releasing tension) without performing the contraction phase.

Whereas our pilot studies demonstrate feasibility and a large effect on sleep outcomes in pwMS following CBT-I [28,29], a well-designed adequately powered prospective randomized control trial (RCT) is needed to assess the efficacy of CBT-I delivered via telehealth compared to an appropriate control group to improve sleep outcomes (Aim 1) and fatigue and health-related quality of life (Aim 2). Also, determining the participant characteristics that predict improvement in sleep outcomes (Exploratory Aim 3) would help guide health care providers and individuals with MS to select an appropriate sleep intervention at an individual level.

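### The adherence percentage credits only getting out of bed, although the programme directs some participants to use an in-bed technique, so those who fully comply lose credit in exploratory Aim 3

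*Protocol article*

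**What the plan says.** Section 2.5 (Secondary Outcomes, item 5) takes adherence to CBT-I from the sleep log. The three items are:

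- rise time: "number of mornings per week the participant got out of bed at agreed upon time"
- stimulus control: "number of times got out of bed if unable to sleep within 20 min"
- wind-down: "number of nights per week the participant conducted wind-down routine"

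They are combined into one figure: "A total percentage will be calculated and used as the outcome of interest". Table 2, under section 2.6, gives the same definition: "number of times got out of bed if unable to sleep within 20 min, number of nights/week conducted wind-down routine; a percentage will be calculated". Neither place states weights or a denominator, and neither mentions an alternative form of the stimulus-control item.

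The programme does have an alternative form. In section 2.7.1, Session 1 covers stimulus control with the instruction "if fall risk, perform counter-control in bed instead". The Introduction, listing the adaptations made for people with MS in the pilot trials, says that "stimulus control was modified to perform a relaxation or distraction technique in bed". It applies this to people with limited function or mobility, and where either the participant or the provider worries about falls.

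Section 3.2.3 (Exploratory Aim 3) models responder status at 6 weeks, an ISI change of at least 6 points, by logistic regression. Disability and intervention adherence are both among the predictors. The hypothesis is that higher disability and lower adherence each go with non-response.

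**The concern.** The adherence measure and the treatment it measures do not match. For participants given the in-bed technique, following the instruction means not getting up, and the score counts only getting up.

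The mismatch does not fall at random. The in-bed form goes to people with mobility limits or fall concern, and Table 1 admits participants up to 6 on the PDDS, so such people can enrol. Their adherence is lowered by the scoring and not by their behaviour, and the lowered value then enters the Aim 3 model next to disability. An association between adherence and response could then partly reflect who was assigned the in-bed form. The adherence percentage is also a listed outcome, so its descriptive summary would be understated.

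**Working it through.** The article reports no adherence value, so there is no figure to reproduce. The check scores one week for a participant who complies fully with the instruction given, under each plausible scoring rule.

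**Inputs.** From section 2.5: rise time and wind-down are counted in days per week, so each has a maximum of 7. Assumed: rise time 7/7, wind-down 7/7, and *k* occasions awake for more than 20 minutes. Let *g* be the number of times the participant gets up. Then *g = k* for a mobile participant following the out-of-bed instruction, and *g = 0* for a participant following the in-bed instruction.

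**Assumed scoring rules.**

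- Per night, averaged: (7/7 + *g*/7 + 7/7)/3. Pooling gives the same value: (7 + *g* + 7)/21.
- Per occasion, averaged: (7/7 + *g*/*k* + 7/7)/3.
- Per occasion, pooled: (7 + *g* + 7)/(14 + *k*).

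**Results.**

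| Fully compliant participant | Per night | Per occasion, averaged | Per occasion, pooled |
|---|---|---|---|
| Mobile, *k* = 4, *g* = 4 | 18/21 = 86% | 3/3 = 100% | 18/18 = 100% |
| In-bed form, *k* = 4, *g* = 0 | 14/21 = 67% | 2/3 = 67% | 14/18 = 78% |
| Good sleeper, *k* = 0 | 14/21 = 67% | 0/0, undefined | 14/14 = 100% |

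For the in-bed form, the pooled per-occasion score is 14/(14 + *k*): 14/15 = 93% for *k* = 1, 14/16 = 88% for *k* = 2, 14/18 = 78% for *k* = 4, and 14/21 = 67% for *k* = 7.

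**Reading the table.** The second row is below 100% under every rule. The loss caused by the mismatch is the gap between the first two rows, since both participants did all that was asked. At *k* = 4 the gap is 86 − 67 = 19 points per night, 100 − 67 = 33 points per occasion averaged, and 100 − 78 = 22 points per occasion pooled. The good-sleeper row has no such stable result: it is 67%, undefined or 100% depending on a denominator that the article does not give.

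**After the fix.** If the assigned form is credited per occasion and the item is omitted when *k* = 0, the three rows become 3/3, 3/3 and 2/2. All are 100%.

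**The case against.** The strongest reply is that a condensed article need not give a scoring manual. Denominators and weights can sit in the full protocol or the analysis plan, the sleep log is not shown, and nothing says outright that in-bed counter-control scores zero. As far as missing weights and denominators go, this is right, and no point is made of them here. It does not dispose of the mismatch. The item is written out twice as getting out of bed, with no exception, while the article itself describes the in-bed form. The loss of credit also appears under every denominator tried.

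Three stronger readings are tempting, and the article does not support them.

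- A reader might infer that full compliance is classed as non-adherence. It is not: the other two items still count, and no adherence cut-off is defined.
- A reader might infer that good sleepers are penalised because they have no occasion to get up. That needs a fixed per-night denominator. The item is conditional on being awake, which fits a per-occasion denominator at least as well, and then a good sleeper gets full marks or an undefined item.
- A reader might infer that disability and adherence become inseparable in Aim 3. The in-bed form follows functional limitation or fall concern, not the PDDS score as such. If disability is in the same model, part of the shared variation is adjusted for. Part may remain, because fall concern is not the same as PDDS.

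It is also fair to say that adherence is observed after randomisation, so its association with response is not a clean causal effect under any scoring. The fix removes one avoidable distortion and does not change that.

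**Conclusion.** The point holds in a limited form. As written, the stimulus-control item gives no credit for the in-bed technique that the programme prescribes to some participants. Someone who follows that instruction fully loses credit in any week with at least one occasion awake for more than 20 minutes. The loss is up to about one third of the score if the three items are equally weighted, which is an assumption. Under pooled per-occasion scoring the total is 93% to 67% for 1 to 7 occasions a week.

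The share of participants given the in-bed form is not stated, so neither the size nor the net direction of the effect on the Aim 3 coefficients can be worked out. What can be said is that low adherence is partly tied to disability or fall concern through the scoring. The consequence is confined to the adherence summary and exploratory Aim 3. The ISI analysis and the sample size are untouched. It should be corrected before Aim 3 is analysed.

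**What to change.** Reconcile the adherence definition in section 2.5 and Table 2 with the programme described in section 2.7.1 and the Introduction. This concerns scoring only, and no view is taken on which stimulus-control instruction is right.

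- Score the item as occasions on which the participant used the form assigned to them (out of bed or in bed), divided by occasions awake for more than 20 minutes.
- Omit the item when there are no such occasions, and base the percentage on rise time and wind-down.
- Record in the log which form was assigned and whether the in-bed technique was used.
- If either was not recorded for some participants, use the two-item score (rise time and wind-down) for all participants in Aim 3. Scoring some on two items and others on three would put two definitions into one predictor.

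The cost is one added log item and a written scoring rule. If the two-item score has to be used, the adherence measure is somewhat less complete, because it no longer reflects stimulus control.
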